### Enrolment and randomisation

After participants provide their written informed consent (which will also be obtained from a parent or legal guardian if the participant is younger than 18 years of age), they will undergo a baseline assessment in which they will be screened for eligibility. Participants will be randomised to either the CBT + FLX or CBT + PBO group in a 1:1 ratio, sequentially as they become eligible for randomisation. The randomisation will be stratified by site (OYHCP and *headspace* centres), age (≤18 and >18 years) and sex, and randomly permuted blocks (of sizes 2, 4 and 6) will be programmed into the electronic case report form by an independent statistician. The investigators, research assistants, study biostatistician, clinicians and participants will all be blinded with respect to randomisation. Only the pharmacist will be aware of the group to which the participant has been allocated. Participants can be unblinded in emergency situations when it is important that medical staff know which medication the participant has received. If unblinded, the participant’s treatment in the study will then be discontinued. Participants whose study medication treatment is discontinued will continue to be assessed at the scheduled times, provided they have not withdrawn their consent. Participants will be unblinded by the treating doctor after the 12-week period so that the doctor can make appropriate clinical decisions about the participant’s continuing management.

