### Statistical methods and determination of sample size

Primary analyses will be undertaken on an intention-to-treat basis, including all participants as randomised, regardless of treatment actually received. The CBT + FLX group will be compared with the CBT + PBO group using a planned contrast of change from baseline to the week 12 endpoint on the basis of MADRS scores within a mixed-model repeated measures analysis [55]. Stratification variables will be evaluated and retained in analyses where they are measured as significant or quasi-significant. An unconstrained variance–covariance matrix will model within-individual dependencies. Transformation of scores, including categorisation, may be undertaken to meet distributional assumptions and accommodate outliers. Comparisons of changes in MADRS scores from baseline to other time points will be undertaken as secondary analyses.

Models for binary outcomes analogous to the primary analysis approach will be used to compare the remission rates and other dichotomous outcomes between the two treatment arms at endpoints and other occasions of measurement. Relative and absolute risk reduction, number needed to treat [56] and other relevant indices will be calculated for these outcomes. In analyses of scaled secondary variables, methods comparable to those employed in the primary analysis will be used. In exploratory analyses, the effects of moderators and mediators of treatment will be examined. Safety data will be compared between treatment arms—in particular, the rates of suicide-related adverse events—using Fisher’s exact test. All tests will be conducted using a two-sided α level of 0.05 and 95% confidence intervals.

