The primary outcome measure is change on the MADRS at 12 weeks. On the basis of large, previously published fluoxetine trials of adolescent depression, we have estimated the pre–post effect size for fluoxetine to be 0.35. This value is less than the mean effect size of 0.5 reported in previous trials, as we have taken into account the modest effectiveness of the CBT administered in both arms. To sufficiently power the study, and assuming a correlation of 0.5 between baseline and 12-week endpoint measurements, a total sample size of 260 participants will be required. For the secondary outcome measure, remission at 12 weeks, there will be 74% power to detect an improvement in the rate of remission of at least 15% in the CBT + FLX arm, assuming remission in the CBT + PBO arm of 20% (consistent with remission in the TADS study).

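### The factors that stratify the randomisation stay in the models only if they test as significant, so the outcome data choose the primary model; the average cost is small, and one sentence fixes it

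*Protocol article*

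**What the plan says.** Enrolment and randomisation: "The randomisation will be stratified by site" (the youth clinical program and the headspace centres), "age (≤18 and >18 years) and sex, and randomly permuted blocks (of sizes 2, 4 and 6"). Allocation is "in a 1:1 ratio, sequentially as they become eligible for randomisation".

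Statistical methods and determination of sample size: the arms are compared "using a planned contrast of change from baseline to the week 12 endpoint on the basis of MADRS scores within a mixed-model repeated measures analysis", with an unconstrained within-person covariance matrix. The next sentence reads: "Stratification variables will be evaluated and retained in analyses where they are measured as significant or quasi-significant". It refers to analyses in general, so it covers the primary one. The section then extends the same approach to the binary outcomes and to the scaled secondary outcomes. Testing is fixed as follows: "All tests will be conducted using a two-sided α level of 0.05 and 95% confidence intervals".

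The section does not define quasi-significance. It does not say whether the factors are judged singly or jointly, or whether they enter as main effects or by visit.

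**The concern.** Stratified permuted blocks make the arms alike on site, age group and sex. If such a factor predicts the outcome and is left out, the variation that it explains stays in the residual although the design has removed it from the arm comparison. The model-based standard error is then larger than the true one, the interval too wide and the test conservative.

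The stated rule makes inclusion depend on a test of each factor against the outcome. Three factors give 2 × 2 × 2 = 8 candidate primary models, and two analysts with different ideas of quasi-significance could fit different ones. Covariates may also differ between outcomes. For remission, if the model is logistic, odds ratios with and without the strata are different quantities, so the selection step can change what is estimated.

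This is not a detail left to an analysis plan. The protocol states a positive rule. An analysis plan that follows it inherits the problem, and one that fixes the covariates contradicts the protocol.

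**Working it through.** **Inputs from the article.** N = 260, 1:1; blocks of 2, 4 and 6; two-sided α = 0.05; effect size: "we have estimated the pre–post effect size for fluoxetine to be 0.35"; correlation: "assuming a correlation of 0.5 between baseline and 12-week endpoint measurements".

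**Assumptions, because the article gives no figures.** Two site levels, hence 8 strata; equally common strata with equal effects; the three factors jointly explain R² = 0%, 5%, 10% or 20% of the variance of the analysed outcome; quasi-significant means p < 0.10 (0.05 and 0.20 also tried).

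**Step 1: the plan's own sample size.** With r = 0.5, the SD of change is SD × √(2(1 − 0.5)) = SD, so d = 0.35 applies unchanged. At an assumed 80% power (the article states no figure), a two-sample comparison needs 129 per arm, 258 in total, against 260 stated. Power with 130 per arm is 80.6%. No strata enter this calculation.

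**Step 2: how often the rule keeps the factors.**
- No factor prognostic: all three are dropped with probability 0.90³ = 0.73 (simulated 72%).
- Joint R² = 5%: each factor has noncentrality √(260 × 0.0167 / 0.95) = 2.14 and is kept with probability 0.69. All three are kept with probability 0.69³ = 0.33 (simulated 32%). No single model had a majority.
- Joint R² = 10%: noncentrality 3.10, each kept with probability 0.93, all three 0.80 (simulated 79%).
- Joint R² = 20%: all three are kept almost always (simulated 99.7%).

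**Step 3: the bound if all strata were always left out.** The model reports SE ≈ 2/√260 = 0.124. The true SE is 2√(1 − R²)/√260. Actual type I error is 2Φ(−1.96/√(1 − R²)).

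| Joint R² | True SE | SE overstated by | Type I, formula | Type I, simulated |
|---|---|---|---|---|
| 5% | 0.121 | 2.6% | 4.4% | 4.5% |
| 10% | 0.118 | 5.4% | 3.9% | 3.5% |
| 20% | 0.111 | 11.8% | 2.8% | 2.8% |

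**Step 4: the rule itself.** Simulation of a single-endpoint linear model, 5,000 trials per null scenario and 2,500 per power scenario:

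| Joint R² | Type I, always in | Type I, kept at p < 0.10 | Power, always in | Power, kept at p < 0.10 | Power, always out |
|---|---|---|---|---|---|
| 0% | 5.2% | 5.2% | not run | not run | not run |
| 5% | 5.0% | 5.0% | 82.7% | 82.7% | 81.0% |
| 10% | 4.7% | 4.7% | 85.3% | 85.3% | 82.3% |
| 20% | 5.0% | 5.0% | 88.2% | 88.2% | 83.2% |

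Over cut-offs 0.05, 0.10 and 0.20, type I error ranged from 4.6% to 5.2%, and power differed from always adjusting by less than 0.1 points (largest gap 82.72% against 82.64%). Taking the smallest p-value over all 8 models gave at most 5.3%. The simulation standard error of a 5% rate is √(0.05 × 0.95 / 5,000) = 0.3 points.

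**Step 5: does a stratum term reach the primary contrast?** If baseline MADRS is one of the repeated occasions, a stratum effect that is constant over time shifts baseline and week 12 equally and cancels from the change. One simulated complete dataset (N = 260, four occasions, unstructured covariance, arm by time, maximum likelihood) gave:
- no strata: contrast −0.4346, SE 0.1231
- strata as main effects only: −0.4346, SE 0.1231 (identical to rounding error)
- strata by visit: −0.4268, SE 0.1189

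Only the stratum-by-visit terms moved the estimate and its standard error.

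**The case against.** The strongest reply is that the rule works well enough. It keeps a factor when the data show it to be prognostic, so omission is uncommon where it would cost most: a factor that explains 4% of variance, with 12% for the three together, has noncentrality √(260 × 0.04 / 0.88) = 3.44 and a 96% chance of being kept at p < 0.10. Selection looks at the factor's own p-value and not at the arm effect, and the study biostatistician is blinded, so there is little room to steer the result. The MADRS time points can all be contrasts from one model, so they need not carry different covariates. All of this stands.

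Step 5 adds that, on a natural reading of the primary model, keeping or dropping strata as main effects cannot change the primary p-value when data are complete. That stands too, within limits: missing data or interaction terms break the equality, and the article does not say how strata would enter.

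A reader might infer from the bound in Step 3 that the trial will run at a type I error of 2.8% to 4.5% and lose up to about 5 points of power (88.2% against 83.2%). The document does not support that. Those figures describe always omitting the strata, which is not the stated rule. Nor is there support for inferring inflated false positives: even the most favourable of the 8 models gave at most 5.3%.

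The exact cut-off alone could be left to an analysis plan. Letting significance decide at all is fixed in the protocol, and that part of the point is not answered.

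**Conclusion.** The point holds as a matter of pre-specification and consistency with the design, at low to moderate severity. The article randomises within strata and then lets outcome data decide whether the analysis recognises them, with no threshold. If the factors are weakly prognostic (5% of variance jointly), the full design-based model would be fitted in only about a third of trials. The average numerical cost is close to nil: type I error about 5% and power within about 0.1 points of always adjusting. The test is conservative only in those cases where a prognostic factor is dropped.

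These sizes rest on assumed stratum effects, two site levels, a single-endpoint linear model standing in for the repeated-measures model, and no missing data. The conclusion that the model is not fixed in advance rests on the text alone.

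**What to change.** Replace the retention sentence with:

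> *Site, age group (≤18, >18) and sex, as used in the randomisation, are included in the primary and all secondary models regardless of significance. In the repeated-measures models they enter with their interactions with visit (or as covariates in a model of change from baseline). The same factors are included in the binary-outcome models.*

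The visit interactions are needed: on the reading in Step 5, main effects alone would leave the primary contrast as it is.

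Cost: one sentence and no new data. In a model of change, the intercept, arm and three binary factors leave 260 − 5 = 255 degrees of freedom; more site levels or visit interactions use a few more. Sparse cells are possible in the binary models, so state in advance what is done if one does not converge. N stays at 260, because the sample-size calculation uses no strata. The article reports enrolment as continuing at submission, so the change could be made before outcomes are analysed.

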## Discussion

Depression is the single greatest cause of morbidity among adolescents and young adults and has a significant influence on the development of an affected person’s social relationships and vocational skills. Its effects are felt across the life course, with substantial costs to the affected individuals, their families and the community. The optimal treatment for depression during adolescence and early adulthood is a source of considerable uncertainty, creating a dilemma for clinicians as to what they should recommend to their patients as first-line treatment. In the present study, we seek to address this issue by conducting a simple, practical clinical trial, the outcomes of which have the potential to substantially influence clinical practice. If the trial shows that fluoxetine provides additional clinical benefits when administered in combination with CBT, it will support first-line use of combined treatment for young people with moderate to severe depression. If, on the other hand, no evidence of any additional benefit is demonstrated, then the current advice to withhold medication will be given empirical support.

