### The effectiveness of antidepressant medications

The effectiveness of antidepressant medications for child and adolescent depression was brought into question by a meta-analysis by Whittington and colleagues [11]. They included both published and unpublished randomised control trials in their meta-analysis and reported that only fluoxetine demonstrated a favourable risk–benefit profile and that sertraline, paroxetine, citalopram and venlafaxine had risk–benefit profiles which were either weak or unfavourable. In a subsequent meta-analysis, Bridge and colleagues [12] reached similar conclusions. They reported a mean effect size of 0.25 (95% CI, 0.16 to 0.34) for antidepressant medications compared with placebo in the treatment of child and adolescent depression, with the fluoxetine trials showing an almost twofold greater effect size of 0.46 (95% CI, 0.29 to 0.62) [12]. In a recent Cochrane review [13], which included trials of all selective serotonin reuptake inhibitors (SSRIs) and newer classes of antidepressants, the authors confirmed that the effects of antidepressant medications for youth depression were small but significant, with rates of remission increasing from 380 per 1,000 for placebo to 448 per 1,000 for medication. It is unclear why fluoxetine appears to be the most effective of the SSRIs in this population, given their similar pharmacodynamics. It might be that fluoxetine’s considerably longer half-life tempers the effects of inconsistent adherence to medication, which can be particularly problematic for young people [14]. Other evidence suggests that the difference is likely to be artefactual. In their recent Cochrane review [13], the authors implemented subgroup analysis to robustly investigate whether the effects of medication were modified by the type of antidepressant. They found no evidence for this hypothesis and concluded that it was premature to assert that fluoxetine is the most effective antidepressant for adolescent depression—especially given that there have been no head-to-head trials.

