Concerns about the efficacy and safety of antidepressant medications for youth depression have led to the development of treatment guidelines that provide only qualified support for their use. The United Kingdom’s National Institute for Clinical Excellence guideline states that psychotherapies should be offered as first-line treatment and that medication should be considered only for moderate to severe depression when there has been insufficient response to psychological therapy [29]. In Australia, the National Health and Medical Research Council guideline also states that psychotherapies should be the first-line treatment, but that fluoxetine should be considered when the patient’s depression is severe, when there has been no response to psychotherapy or when psychotherapy is unavailable [30]. The Australian guideline acknowledges the uncertainty about the use of medications for young people, stating, ‘Many clinically relevant questions remain unanswered by current research evidence, including when a health professional should recommend medication, for whom and at what severity of depression, for how long it should be taken, and how best to monitor progress’ (p 53).

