## Methods/Design

### Study design and ethical approval

The study design is a 12-week, parallel-group, double-blind, randomised control trial in which participants with moderate to severe MDD will be allocated to treatment with either CBT and fluoxetine (CBT + FLX) or CBT and placebo (CBT + PBO). The primary hypothesis is that, after 12 weeks of treatment (the trial endpoint), the CBT + FLX group will show greater improvement than the CBT + PBO group in depressive symptoms compared to baseline. The primary outcome measure we will use is the Montgomery-Åsberg Depression Rating Scale (MADRS), an observer-rated depression scale used widely in depression treatment trials because it is both efficient to administer and psychometrically sound [44]. Our secondary hypotheses are that the CBT + FLX group will show greater improvement than the CBT + PBO group on secondary clinical outcomes, functioning, quality of life (QoL) and safety measures at 12 weeks. Assessments will be completed at baseline and at weeks 4, 8 and 12, with follow-up assessment completed by telephone at week 26. All participants will receive manualised CBT, which will be offered weekly to participants for a period of 12 weeks. The study was approved by the Melbourne Health Human Research Ethics Committee (EC00243) in October 2012.

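### The Discussion reads a null result as support for withholding medication, although a non-significant result in this trial can still be compatible with the full planned benefit

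*Protocol article*

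**What the plan says.** Under Study design and ethical approval, the primary hypothesis is one of superiority: "the CBT + FLX group will show greater improvement than the CBT + PBO group in depressive symptoms compared to baseline". Under Statistical methods and determination of sample size, the test is set by "All tests will be conducted using a two-sided α level of 0.05 and 95% confidence intervals". The size of the trial rests on three statements in that section: "we have estimated the pre–post effect size for fluoxetine to be 0.35", "assuming a correlation of 0.5 between baseline and 12-week endpoint measurements" and "a total sample size of 260 participants will be required". No power figure is given for the primary outcome.

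The Discussion then maps results to practice. A positive trial will support first-line combined treatment. If, on the other hand, "no evidence of any additional benefit is demonstrated, then the current advice to withhold medication will be given empirical support". No third, inconclusive outcome is mentioned.

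On what current advice is, the Background reports two guidelines. The UK guideline keeps medication for moderate to severe depression that has not responded sufficiently to psychological therapy. The Australian guideline says that "psychotherapies should be the first-line treatment, but that fluoxetine should be considered when" depression is severe, psychotherapy has not worked, or psychotherapy is unavailable.

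**The concern.** In a superiority trial tested at 0.05, the natural operational meaning of no benefit being demonstrated is that the primary comparison is not significant. Such a result can arise because there is no useful benefit, or because the estimate is too imprecise to tell. The Discussion sentence does not separate the two. It treats both as positive support for one clinical policy.

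This sentence is the article's only stated route from a null result to practice, and the same paragraph says that the outcomes could substantially influence clinical practice. If it were carried into the results paper, an inconclusive trial could be presented as evidence against combined treatment.

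**Working it through.** **Inputs.** From the sample size paragraph: effect 0.35 SD, correlation r = 0.5, N = 260. From Enrolment and randomisation: 1:1 allocation, so 130 per arm. From the statistical methods: two-sided α = 0.05 with 95% intervals. I take 0.35 as the standardised between-arm difference in change, because that reading reproduces the stated N.

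**Reproducing 260.**
- Change score: SD of change = SD × √(2(1 − 0.5)) = 1 SD. Per arm, n = 2 × (1.960 + 0.842)² / 0.35² ≈ 128.1, so 129, total 258 at 80% power. With 260 the power is 80.6%.
- Baseline-adjusted: residual SD = √(1 − 0.5²) = √0.75 SD. Per arm, n = 2 × 0.75 × (1.960 + 1.282)² / 0.35² ≈ 128.7, so 129, total 258 at 90% power. With 260 the power is 90.3%.

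The stated N is therefore consistent with about 80% or about 90% power, and the article does not say which. Both readings are carried forward.

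**Precision of the result.**
- Change score: SE = √(2/130) = 0.124; half-width = 1.96 × 0.124 = 0.243.
- Baseline-adjusted: SE = 0.124 × √0.75 = 0.107; half-width = 0.211.

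An estimate is non-significant if it lies below the half-width (for positive estimates). Its interval contains 0.35 if it lies above 0.35 minus the half-width. The largest upper limit of a non-significant result is twice the half-width.

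| | Change score | Baseline-adjusted |
|---|---|---|
| Estimates that are non-significant with an interval containing 0.35 | 0.107 to 0.243 | 0.139 to 0.211 |
| Largest upper limit of a non-significant result | 0.486 | 0.421 |
| Chance of a non-significant result if the true effect is 0.35 | 19.4% | 9.7% |
| Share of those results whose interval contains 0.35 | 87% | 74% |

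**Dropout.** The article states none. Assuming 20% loss (104 per arm) on the change score, the half-width is 1.96 × √(2/104) = 0.272, power falls to 71%, and a true effect of 0.35 is missed about 29% of the time.

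**What a null trial could legitimately show.** If the true effect is zero, the chance that the interval excludes a benefit d is Φ(d/SE − 1.96). On the change score:
- d = 0.35: Φ(0.35/0.124 − 1.96) = 81%.
- d = 0.175 (half the planned effect): Φ(0.175/0.124 − 1.96) = 29%. Reaching 80% would take 1026 participants.

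Baseline-adjusted, the figure for 0.35 is Φ(0.35/0.107 − 1.96) ≈ 90%.

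**The same point for remission.** The article gives 74% power for a 15-point gain over 20%, so a true gain of that size is missed 26% of the time. An observed 20% v 30% has SE = √((0.16 + 0.21)/130) = 0.053 and a 95% interval of −0.5 to 20.5 points. That is non-significant, yet the interval contains the planned 15 points.

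**The case against.** The strongest reply is that this is a closing sentence in a Discussion and not an analysis rule. The statistical methods contain no such decision rule and promise 95% intervals, so readers would see whether 0.35 is excluded. The sentence also speaks of no evidence of any benefit, which could be read across several outcomes, and an estimate near the significance boundary is hardly no evidence. All of this limits the point: no analysis changes, and the percentages above are chances of a non-significant primary comparison, not established chances that the authors would draw the negative conclusion. It does not remove the point, because the sentence positively states an inference that the design does not license and leaves no room for an inconclusive result.

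Several stronger readings are tempting but not supported:
- A reader might infer that the trial is too small. It is not shown to be: 260 reproduces under conventional power, and the 10% to 20% miss rate is simply its ordinary type II error.
- A reader might quote only the change-score figures, or set the upper limit against the 0.46 that the Background gives for the fluoxetine trials. With baseline adjustment the limit is 0.42, so that comparison fails on one of the two admissible readings.
- A reader might take the Background's all-antidepressant mean ("They reported a mean effect size of 0.25") as the true effect here. It comes from comparisons with placebo in children and adolescents, whereas the sample size paragraph discounts for CBT given in both arms.
- A reader might fault the article for giving no smallest worthwhile difference. That could stand in a fuller document not shown; only the wording of the Discussion is at issue.
- A reader might infer that the Discussion misdescribes current advice altogether. It is fair shorthand for first-line treatment under the UK guideline. The mismatch is confined to the Australian guideline, mainly in severe depression, which this trial of moderate to severe illness includes.

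**Conclusion.** The point holds under both readings of the unstated power. As worded, the Discussion lets a non-significant result count as support for withholding medication, when such a result can have an interval reaching 0.49 SD (change score) or 0.42 SD (baseline-adjusted), above the planned 0.35 SD in either case. A true effect of 0.35 SD would be missed about 20% or 10% of the time with complete data.

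This rests on 0.35 being a between-arm effect in SD units, r = 0.5, equal arms and normal approximations. The 29% figure rests in addition on an assumed 20% loss.

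Not every null result is uninformative. Estimates below 0.107 SD (change score) or 0.139 SD (baseline-adjusted) exclude 0.35. But 0.35 is an expected effect and not shown to be the smallest worthwhile one, so excluding it is the least that a negative conclusion should require. For example, a change-score estimate of 0.10 has an interval of −0.14 to 0.34. That excludes 0.35 but leaves 0.25 possible.

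**What to change.** Reword the Discussion along these lines: *If the 95% confidence interval for the difference in MADRS change at week 12 excludes a benefit of X points, the result supports not adding fluoxetine to first-line CBT. If the result is non-significant and the interval includes a benefit of X points, it is inconclusive.* Here X is the smallest worthwhile benefit, fixed in MADRS points before the treatment comparison is unblinded and no larger than the planned 0.35 SD. Enrolment was continuing when the article was submitted, so this could still be settled ahead of the results.

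In the same edit, reconcile the phrase about current advice with the Background's account of the Australian guideline for severe depression.

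The cost is wording only: the 95% intervals are already planned, and neither the sample size nor the analysis changes. The real price is that some null results must be called inconclusive, and more of them as X falls below 0.35 SD. On the change score with no true effect, 260 participants exclude 0.35 SD about 81% of the time but 0.175 SD only about 29%.
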